# Ultrasound-guided supraclavicular block versus Bier block for emergency reduction of upper limb injuries: a protocol for an open-label, non-inferiority, randomised controlled trial

**DOI:** 10.1186/s13063-023-07403-z

**Published:** 2023-05-30

**Keywords:** Supraclavicular block, Nerve block, Bier block, Regional anaesthesia, Emergency medicine, Randomised controlled trial, Ultrasonography, Upper limb injury, Pain

## Abstract

**Background:**

Closed reduction of upper limb fractures and/or dislocations are common in the emergency department (ED), which involves physically re-aligning the injured part prior to immobilisation. As this is painful, numerous techniques are available to provide regional anaesthesia to ensure patient tolerance. A Bier block (BB) is typically performed as part of routine care. An alternative technique gaining interest in the ED is ultrasound-guided supraclavicular block (UGSCB), which involves injecting local anaesthetic around the brachial plexus at the supraclavicular fossa under ultrasound guidance. It is unclear whether UGSCB is effective and safe when performed in the ED.

**Methods:**

SUPERB (SUPraclavicular block for Emergency Reduction versus Bier block) is a prospective open-label, non-inferiority randomised controlled trial that compares the effectiveness of UGSCB versus BB for closed reduction of upper limb fractures and/or dislocations. Adult patients presenting with an upper limb fracture and/or dislocation that requires emergent closed reduction in the ED will be eligible. After screening, participants will be randomised to either UGSCB or BB. Once regional anaesthesia is obtained, closed reduction of the injured part will be performed and appropriately immobilised. The primary outcome is maximal pain experienced during closed reduction measured via a visual analogue scale (VAS). Secondary outcomes include baseline and post-reduction pain, patient satisfaction, total opioid requirement in ED, ED length of stay, adverse events and regional anaesthesia failure.

**Discussion:**

Existing evidence suggests UGSCB is effective when performed in the operating theatre by trained anaesthetists. SUPERB will be the first randomised controlled trial to elucidate the effectiveness and safety of UGSCB in the ED. The findings have the potential to provide an alternative safe and effective option for the management of upper extremity emergencies in the ED.

**Trial registration:**

This trial has been registered on 21 October 2022 with Australia and New Zealand Clinical Trials Registry (ACTRN12622001356752).

## Administrative information

Note: the numbers in curly brackets in this protocol refer to SPIRIT checklist item numbers. The order of the items has been modified to group similar items (see http://www.equator-network.org/reporting-guidelines/spirit-2013-statement-defining-standard-protocol-items-for-clinical-trials/).

## Introduction

### Background and rationale {6a}

Closed reduction of upper limb fractures and/or dislocations are commonly performed in the emergency department (ED). This involves physically manipulating the injured part to restore anatomical alignment prior to immobilisation. As this is a painful procedure, there are numerous techniques available to provide regional anaesthesia to ensure patient comfort and tolerance. Bier block (BB) has traditionally been advocated as the preferred technique in the ED, where intravenous (IV) injection of local anaesthetic is performed to the injured limb with a tourniquet applied proximally to prevent systemic spread [1]. This anaesthetises the upper limb distal to the tourniquet. BB is considered routine care across many Australian EDs [2], but is often associated with discomfort from the tourniquet pressure, limited by numerous contraindications, and there can be difficulty obtaining IV access on the injured limb due to swelling and/or bruising [3]. Procedural sedation with IV agents is an alternative option if there are contraindications to BB, but this can be resource intensive with risk of adverse effects, particularly in patients with multiple co-morbidities [4].

An alternative regional anaesthetic technique gaining traction in the ED is the ultrasound-guided supraclavicular block (UGSCB; [5]). Using ultrasound, the brachial plexus that innervates the upper limb at the supraclavicular fossa is identified. A needle is inserted to infiltrate local anaesthetic around these nerves under direct visualisation [6], which results in anaesthesia of the ipsilateral arm. UGSCB has numerous advantages in the ED including familiarity of the anatomy of the supraclavicular region amongst emergency physicians due to ultrasound-guided central venous line placement, its relative ease of being performed, potential for prolonged analgesia and relatively low incidence of complications [7, 8]. Evidence supporting the effectiveness of UGSCB has been performed predominantly in the operating theatre by anaesthetists for surgical management of upper limb injuries [9, 10]. However, it remains unclear whether UGSCB, when performed by emergency physicians in the ED, is an effective and safe alternative for providing regional anaesthesia for closed reduction of upper limb fractures or dislocations. Therefore, the objective of this trial is to evaluate whether the pain associated with limb reduction after UGSCB is non-inferior in comparison to that after BB in the ED, using a randomised controlled trial design.

### Objectives {7}

The primary objective of the SUPraclavicular block for Emergency Reduction of upper limb injuries versus Bier block (SUPERB) trial is to determine the effectiveness of UGSCB for providing regional anaesthesia for closed reduction of upper limb fractures and/or dislocations in the ED compared to BB, with a non-inferiority hypothesis for patient reported procedural pain. The secondary objectives are to assess post-reduction pain, patient satisfaction, total opioid requirement in ED, ED length of stay, adverse events and regional anaesthesia failure following UGSCB with comparison to BB.

### Trial design {8}

SUPERB is an open-label, single-site, non-inferiority randomised controlled trial (RCT), with a 1:1 allocation ratio. The protocol adheres to the Standard Protocol Items: Recommendations for Interventional Trials (SPIRIT) Statement.

## Methods: Participants, interventions and outcomes

### Study setting {9}

SUPERB will be conducted at Redland Hospital ED, which is an urban district hospital in Brisbane with an annual census of ~ 55,000 presentations. There is limited on-site orthopaedic service during the weekdays and no inpatient orthopaedic service after hours or on weekends (with patients either managed in ED or transferred to the nearest centre during these times). There are ~ 100 upper limb reductions performed in our ED annually.

### Eligibility criteria {10}

Potentially eligible participants will be approached and invited to participate in the study by the research investigator, research assistant or treating clinician. The inclusion and exclusion criteria are outlined in Table 1, with the main criteria being adults presenting to ED with an upper limb fracture and/or dislocation requiring closed reduction with no contraindication to either method of regional anaesthesia. Patients who are screened and excluded will be noted, including the comparison of contraindications due to either technique.

**Table 1 Tab1:** Inclusion and exclusion criteria

Inclusion criteria	Exclusion criteria
• Aged 18 or older • Capacity to provide informed written consent • Upper limb fracture and/dislocation requiring ED closed reduction and immobilisation	• Refusal to consent • Local anaesthetic allergy • Open fractures, unstable fracture and/or dislocations that require urgent surgical fixation • Pregnancy • Anticoagulation • Chronic lung disease (e.g., chronic obstructive pulmonary disease or unstable asthma) • Skin infection over the supraclavicular site of injection • Previous surgery or radiation therapy to the supraclavicular region • Severe hypertension (> 160 mmHg) • Compartment syndrome • Congenital or idiopathic methaemoglobinaemia • Sickle cell disease • Peripheral vascular disease • Peripheral neuropathy • Cardiac conduction abnormality

### Who will take informed consent? {26a}

Once patients are deemed eligible for the study (after confirmation of forearm or elbow fracture/dislocations on X-ray and satisfying the inclusion and exclusion criteria), they are approached to participate in the trial by the treating clinician or a member of the research team. An information sheet outlining the research study will be provided. Written informed consent will be obtained by a member of the research team (research investigator or assistant) or the treating emergency physician.

### Additional consent provisions for collection and use of participant data and biological specimens {26b}

There are no plans for ancillary studies in the future using the data collected in this trial.

## Interventions

### Explanation for the choice of comparators {6b}

#### Bier block

In many EDs, BB remains the standard option for providing regional anaesthesia to allow for painful procedures involving the upper limb to be undertaken [2]. A BB will be performed by a qualified emergency physician (i.e. certified by the Australasian College for Emergency Medicine). The participant will be positioned in semi-reclined sitting. Monitoring will include continuous pulse oximetry, five-minute interval blood pressure on an unaffected limb and three-lead electrocardiography (ECG). An intravenous cannula (IVC) will be inserted at the wrist/hand or forearm of the injured limb. A second IVC will be available on the unaffected limb. The BB cuff (AT4, AneticAid, West Yorkshire, United Kingdom) will be applied at the proximal upper limb. The arm is then elevated for five minutes to enhance venous drainage, before the cuff is inflated to 100 mmHg above the patient’s systolic blood pressure (to a maximum of 250 mmHg). Prilocaine (0.5%, 5 mg/kg to maximum of 250 mg) or lignocaine (0.5%, 3 mg/kg to maximum of 200 mg) will be injected via the IVC on the affected side. Adequacy of the block will be assessed by the treating clinician prior to closed reduction of the injured part and immobilisation. The BB cuff is then slowly released after 30 min.

### Intervention description {11a}

#### Ultrasound-guided supraclavicular block

UGSCB will be performed by emergency physicians who have obtained competency through a one-hour training workshop and performance of at least two UGSCB under direct supervision of an emergency physician competent in the procedure. To perform UGSCB, participants will be in a semi-reclined sitting position, with their head turned away from the side to be block. Monitoring will include continuous pulse oximetry, five minutely blood pressure on the unaffected limb and three-lead ECG. Aseptic technique will be adhered to including sterile gloves, sterile ultrasound probe cover and sterile gel. The supraclavicular region will be prepared with chlorhexidine and draped. Ultrasound imaging of the supraclavicular fossa will be undertaken using a 12 MHz linear probe (Sonosite X-Porte, Fujifilm, Washington USA) or equivalent. The brachial plexus will be identified, and its relation to the subclavian artery, pleura and first rib. Colour Doppler is used to identify and avoid blood vessels. Local anaesthetic (2–3 ml 1% xylocaine + adrenaline) will be injected using a 25G needle to anaesthetise the overlying skin. A 21 G × 110 mm echogenic needle (Sonoplex II, Pajunk, Geisingen Germany) attached to a 20 ml syringe will be inserted under ultrasound guidance to deposit local anaesthetic (20 ml of 0.75% ropivacaine) inferior and superior to the brachial plexus bundle (Fig. 1). Evidence suggests that a two-injection technique is associated with better regional anaesthesia compared to a single-injection technique [11]. Adequacy of regional block will be assessed by the treating clinician prior to closed reduction of the injured part and immobilisation.

**Fig. 1 Fig1:**
[figure not shown]
Ultrasound-guided supraclavicular block (UGSCB): Left panel illustrating ultrasound probe and needle placement. Right panel showing ultrasound anatomy of the supraclavicular fossa, with superimposed needle trajectories for UGSCB. Abbreviations: BP-Brachial plexus, SA-Subclavian artery, SCM-sternocleidomastoid

### Criteria for discontinuing or modifying allocated interventions {11b}

Should the participant demonstrate inadequate anaesthesia from either UGSCB or BB, as evidenced by the inability to tolerate closed reduction of the injured part, the treating clinician can choose an additional or alternative method that will allow the participant to undergo safe and comfortable closed reduction of the injured limb. The choice of technique will be at the discretion of the treating clinician in consultation with the patient, and may include the use of inhaled nitrous, performing the alternative trial intervention (BB or UGSCB), IV procedural sedation, or abandonment and referral to a centre with theatre access for orthopaedic procedures.

### Strategies to improve adherence to interventions {11c}

Treating clinicians will be educated on the research trial and supported by the research investigators and assistants. A checklist will be utilised to maximise adherence to the intervention protocols.

### Relevant concomitant care permitted or prohibited during the trial {11d}

Participants can receive concomitant analgesia including inhaled nitrous, oral and/or IV analgesia during the study as clinically indicated. The type and/or total dose of analgesia received in the ED will be recorded and compared between the two study groups.

### Provisions for post-trial care {30}

Following closed reduction, the injured part will be typically immobilised with plaster of paris with repeat x-rays performed to assess anatomical alignment of the injured part. After adequacy of reduction, the participant will be discharged from the ED with orthopaedic follow-up within approximately one week for review and ongoing management. In the event where there is inadequate reduction or neurovascular injury requiring urgent treatment, participants will be managed by the acute orthopaedic service. In the event where a participant experiences adverse effects from either BB or UGSCB, they will be managed appropriately by the treating emergency physician in the ED. The type and severity will be compared between groups.

### Outcomes {12}

The primary outcome of the study will be the maximal level of pain experienced during closed reduction of the injured part, as reported by the participant on a 10 cm visual analogue scale (VAS) immediately after completion of the closed reduction procedure. The patient will be asked by the research investigator, research assistant or treating clinician to mark their pain on a VAS scale printed on paper anchored with “no pain” at 0 cm and “pain as bad as it could possibly be” at 10 cm. The 10 cm VAS has been demonstrated previously to be valid and reliable for participant-reported pain [12].

Secondary outcome measures will include:Baseline pain: Participant reported pain will be measured using a 10 cm VAS immediately prior to the commencement of either UGSCB or BB. Any analgesia administered prior to the procedure will be compared between groups to ensure that they are similar.Pain at one hour post-procedure: Participant reported pain at one hour post procedure (or just prior to discharge if under an hour) will be measured using a 10 cm VAS.Patient satisfaction will be measured using a 10 cm VAS satisfaction scale anchored with “extremely dissatisfied” at 0 cm and “extremely satisfied” at 10 cm. This will be measured one hour post procedure (or just prior to discharge if under an hour). The patient satisfaction VAS has been validated to be a reliable tool to evaluate patient satisfaction [13].ED length of stay: the time (minutes) from triage to readiness to be discharged from the ED, will be obtained from the electronic medical record.Analgesia: The total opioid use including those given by the ambulance service pre-hospital and those administered in the ED will be recorded. Total opioid use will be converted to oral morphine milligram equivalent using Australian and New Zealand College of Anaesthetists Faculty of Pain Medicine opioid calculator (http://www.opioidcalculator.com.au).Management: The number of sedations and techniques required in ED, the number of inpatient transfers, and the number of manipulations or operations at another hospital will be compared between groups.Adverse events/complications: Any adverse events experienced by the participant or noted by the treating clinician will be recorded. We will also contact the participant via email 24–72 h after discharge from the ED to evaluate any adverse events post-discharge.Adjunct therapies or treatment failure for UGSCB and BB will also be compared between the two groups.

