## Statistical methods

### Statistical methods for primary and secondary outcomes {20a}

Group data will be used for data and statistical analysis. Data will be summarised as mean (standard deviation) or median (interquartile range) for continuous variables, depending on the normality of their distribution, and as frequency (percentage) for categorical variables. The primary outcome of pain intensity during the procedure will be assessed as a non-inferiority hypothesis using data from the 10 cm VAS tool. The between-group difference in pain intensity will be assessed using linear regression modelling with group allocation (UGSCB vs BB) included as a main effect. A conclusion of non-inferiority will be determined if the 95% confidence interval for the between-group difference in mean maximal pain is entirely below the non-inferiority margin. Analysis will be performed on an intention-to-treat basis, with a per-protocol analysis of the primary outcome also included as a key secondary finding.

For analysis of other secondary outcomes, linear regression modelling will be used to compare continuous outcome data, including between-group difference in patient satisfaction on the 10 cm VAS satisfaction scale and total opiate dose in mg of morphine equivalent. Difference in median procedural time and ED length of stay will be compared using median regression. Odds of dichotomous outcomes will be compared using logistic regression modelling. Formal adjustment for multiplicity will not be performed. Analysis will be performed on Stata (StataCorp, Texas USA), v14.2 or later.

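### The opioid outcome is described as use in the ED but defined to include ambulance and pre-randomisation doses, and the total is compared without adjustment for them (minor, secondary outcome only)

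*Protocol article*

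**What the plan says.** The opioid outcome is described in two ways. The abstract and Objectives {7} refer to "total opioid requirement in ED", and section {11d} on concomitant care compares analgesia received in the ED. Outcomes {12} goes further: "The total opioid use including those given by the ambulance service pre-hospital and those administered in the ED will be recorded". That total is converted to oral morphine milligram equivalents. No section sets a starting point at randomisation or at the block.

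The order of events is clear. Patients are approached "after confirmation of forearm or elbow fracture/dislocations on X-ray and satisfying the inclusion and exclusion criteria", and the abstract states "After screening, participants will be randomised to either UGSCB or BB". Table 2 likewise places screening and consent before allocation.

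The statistical methods {20a} compare total opiate dose between groups by linear regression and name no baseline covariate. Outcomes {12} has analgesia given before the procedure compared between groups as a check of similarity, but does not subtract it or adjust for it.

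Two neighbouring items are relevant. Length of stay is "the time (minutes) from triage to readiness to be discharged from the ED". The methods also state "Difference in median procedural time and ED length of stay will be compared using median regression", although procedural time appears neither in Outcomes {12} nor in Table 2.

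**The concern.** An objective about opioid requirement in the ED and an outcome that adds pre-hospital doses are different quantities under one name, so the reported comparison may not answer the stated objective. Restricting the count to the ED would not settle it, because ED doses given before allocation would still be included.

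Any opioid given before randomisation is fixed before the block is assigned. In an unadjusted comparison of totals it carries no treatment effect and generally adds spread. The Discussion lists lower opioid requirement among the possible added benefits of UGSCB. With about 38 participants per group, a real difference in later opioid use could be harder to see than it need be.

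**Working it through.** **The plan's own figure.** The only sample size calculation concerns the primary outcome (Sample size {14}): margin 20 mm, SD 30 mm, one-sided alpha 0.025, power 80%.

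- n per group = 2 × [30 × (1.960 + 0.842) / 20]² = 35.3, rounded up to 36, so 72 in total.
- 72 / 0.95 = 75.8, rounded up to 76, or 38 per group.

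Both figures reproduce. Neither depends on the opioid outcome.

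**What the unadjusted total does.** Write total = pre + post, split at randomisation. Only post can respond to treatment, so the expected group difference is the same for total and for post. The variance differs:

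Var(total) = Var(pre) + Var(post) + 2 Cov(pre, post).

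Set SD(post) = 1, SD(pre) = r and the correlation = ρ. Then Var(total) = 1 + r² + 2ρr. The documents give neither r nor ρ, so both are assumptions here.

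**Reference effect (assumed).** With 38 per group and a two-sided 5% test, 80% power on post alone corresponds to (1.960 + 0.842) × √(2/38) = 0.64 SD of the post dose. The protocol sets no target difference for opioids.

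**Power for the same effect using the total.** Power = Φ(2.802 / √(1 + r² + 2ρr) − 1.960).

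| r = SD(pre)/SD(post) | ρ = 0 | ρ = +0.3 | ρ = −0.5 | N multiplier at ρ = 0 |
|---|---|---|---|---|
| 0.25 | 78% | 72% | 88% | 1.06 |
| 0.5 | 71% | 61% | 90% | 1.25 |
| 1.0 | 51% | 41% | 80% | 2.00 |
| 1.5 | 34% | 28% | 56% | 3.25 |

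Worked example for r = 0.5, ρ = 0: √1.25 = 1.118; 2.802 / 1.118 − 1.960 = 0.546; Φ(0.546) = 71%.

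**When the total is no worse than the unadjusted post dose.** This needs Cov(pre, post) ≤ −Var(pre)/2, that is ρ ≤ −r/2. It could happen if early doses replace later ones.

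**What adjustment does.** Regressing post on group and pre leaves residual variance 1 − ρ². Compared with the unadjusted total:

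(1 + r² + 2ρr) − (1 − ρ²) = (r + ρ)² ≥ 0.

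Apart from the one degree of freedom spent on the covariate, the adjusted analysis is therefore never less precise than the total, whatever the sign of the correlation. On the same reference effect its power is 80% at ρ = 0, about 84% at ρ = +0.3 (residual variance 0.91) and about 90% at ρ = −0.5 (residual variance 0.75).

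**The case against.** **No bias.** A reader might infer that counting earlier doses can manufacture a treatment effect. The documents do not support that. Randomisation balances the earlier dose on average. A chance imbalance (standard error √(2/38) = 0.23 of its SD) is already reflected in the confidence interval, and the false-positive rate stays nominal. The cost is precision only.

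**Unknown size and direction.** No SD or correlation for opioid dose is given. Under negative correlation the total can even be more precise than the unadjusted later dose, as the table shows. This stands, so a flat statement that precision is lost would go too far. Adjustment covers both directions.

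**Partly handled already.** Pre-procedure analgesia is compared between groups, and covariates for secondary models may be in an analysis plan that is not shown. Comparing for similarity makes an imbalance visible but removes no variance. The conflict between the objective and the definition is in the protocol itself and does not depend on a missing plan.

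**Length of stay.** It may be tempting to say the same of the triage start. But the Discussion frames this aim as a departmental one concerning overall ED stay, and triage to readiness measures exactly that. It is not misdefined. Because it is analysed by median regression, variance-share arithmetic for means does not give its loss of precision either.

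**Transfers.** One might suspect that a failed reduction ends in an early transfer and so looks like a short stay. Nothing in the documents shows this. Further attempts after an inadequate block could equally lengthen the stay, and transfers, sedations and treatment failures are separate outcomes.

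**Procedural time.** Its absence from the outcome list is a listing inconsistency. Since it is not defined, the text gives no ground for calling it a better measure.

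**Conclusion.** The point holds for the opioid outcome. The descriptions in the abstract, Objectives {7} and section {11d} do not match the definition in Outcomes {12}. The planned comparison also includes a part fixed before allocation, for which no adjustment is named. Both follow from the text alone.

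The size of the precision loss does not. The fall from 80% to about 71% to 51% assumes that the earlier dose is uncorrelated with the later one and has 0.5 to 1.0 times its SD. Other assumptions give anything from a gain to a larger loss. Importance is minor: only a secondary outcome is affected, and the primary outcome, its margin and the 76 participants stand.

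**What to change.** 1. Reconcile the abstract, Objectives {7}, section {11d} and Outcomes {12}, so that the opioid outcome has one name and one counting window.
2. Make the between-group comparison the oral morphine equivalent given from randomisation to readiness for discharge, adjusted in the planned linear regression for the dose given before randomisation (ambulance plus ED).
3. Report the all-inclusive total descriptively.
4. Keep triage-to-readiness length of stay as the departmental measure. Optionally add time from randomisation, or adjust for time elapsed before randomisation.
5. List procedural time in Outcomes {12} and Table 2, with its start and stop points.

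The cost is wording plus some data extraction. Each dose must be timed relative to randomisation from the record, because the existing check concerns analgesia before the procedure, which is not the same cut-off. No change to sample size is needed.

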### Participant timeline {13}

Table 2 Shows a schematic of the participant timeline.

**Table 2 Tab2:** Timeline for data collection (SPIRIT Figure)

	Screening	Allocation	Post-allocation			Close-out	
TIMEPOINT	Pre-intervention		Intervention	Closed reduction & immobilisation	Post-intervention	Discharge from ED	Post Discharge from ED
ENROLMENT:							
Eligibility screen	X						
Informed consent	X						
Participant demographics	X						
Randomisation		X					
INTERVENTIONS:							
*UGSCB*			X				
*BB*			X				
Closed reduction & immobilisation				X			
ASSESSMENTS:							
Pain VAS during closed reduction^a^				X			
Baseline Pain VAS	X						
Pain VAS prior to discharge					X		
Patient satisfaction VAS					X		
ED length of stay						X	
Opioid use						X	
Adverse events or complications						X	
Adjunct therapy or treatment failures						X	
Number of sedations and techniques used in ED						X	
Number of inpatient transfers, subsequent sedations, or operations							X

*Abbreviations*: *UGSCB* Ultrasound-guided supraclavicular block, *BB* Bier block, *VAS* Visual analogue scale, *ED* Emergency department

^a^Primary outcome

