### Plans to promote participant retention and complete follow-up {18b}

The collection of primary and secondary outcome data will occur before, during and after the allocated intervention and closed reduction during the index ED presentation, as well as from routine medical records obtained during that presentation. As data is obtained during the same clinical event as participant recruitment, rates of attrition are expected to be low. Should a participant elect to withdraw from the study, no further additional information will be collected, although non-identifiable data such as pain scores already collected will be retained to ensure the result of the study can be measured.

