### Adverse event reporting and harms {22}

Potential harm from UGSCB and BB are listed in Table 3.

**Table 3 Tab3:** Potential harm/adverse effects

UGSCB	BB
Pain during injection and bruising	Pain during insertion intravenous catheter
Infection	Discomfort of cuff inflation
Injury to major blood vessels or nerves	Infection
Puncture of the lungs	Local bruising
Respiratory distress from phrenic nerve paralysis	Methaemoglobinaemia
Local anaesthetic toxicity	Local anaesthetic toxicity

*UGSCB* Ultrasound-guided supraclavicular block, *BB* Bier block

The occurrence of potential adverse events will be systematically checked from a list and prospectively recorded on the clinical research form. Additionally, other adverse events will be captured from the open-ended question “Were there any other adverse events not listed?” All harms encountered in the trial will be reported in the final report. The principal investigator will report any serious events to the institutional HREC within 72 h of the notice.

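### The last stated adverse-event contact is one email 24–72 h after discharge, although Table 3 names infection and nerve injury and an orthopaedic review is already planned at about one week

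*Protocol article*

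**What the plan says.** - **Outcomes {12}.** Adverse events noted by the participant or clinician are recorded. After that, "We will also contact the participant via email" 24–72 "h after discharge from the ED to evaluate any adverse events post-discharge". No later adverse-event contact is stated anywhere in the article.
- **Adverse event reporting and harms {22}, Table 3.** Infection is listed under both blocks. "Injury to major blood vessels or nerves" is listed under UGSCB only. Harms are sought with a checklist and an open question.
- **Provisions for post-trial care {30}.** Once the reduction is adequate, "the participant will be discharged from the ED with orthopaedic follow-up within approximately one week for review and ongoing management". The limb is typically in plaster. No section uses that review as a source of adverse-event data.
- **Participant timeline {13}, Table 2.** The adverse-event row is marked at ED discharge only. The only row marked after discharge is "Number of inpatient transfers, subsequent sedations, or operations", with no time window.
- **Retention and follow-up {18b}.** Outcome data come from the index presentation, "as well as from routine medical records obtained during that presentation". The email is not mentioned.
- **Background {6a} and Discussion.** UGSCB is credited with "potential for prolonged analgesia and relatively low incidence of complications", and the Discussion adds possible medium-term analgesia. The Abstract and Discussion say the trial will establish the safety of UGSCB in the ED as well as its effectiveness.

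**The concern.** The trial names certain harms as risks of the blocks and then makes its last enquiry about them at a time that may not suit them.

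- **Infection.** Infection at a puncture site may not be apparent on day 1–3.
- **Nerve injury.** An emailed self-report from someone with a plastered limb, after a block expected to give lasting analgesia, may not separate residual block or the effects of the injury and cast from a new deficit. It cannot show whether a deficit persists.

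Adverse events are a secondary objective, and the article expects the results to bear on whether UGSCB is a safe option in the ED. A low count of these harms would be hard to interpret if nobody was asked after day 3.

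The article also disagrees with itself on whether anything is collected after discharge. Outcomes {12} says yes, while Table 2 and {18b} do not show it. A site working from Table 2 could omit the email altogether.

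**Working it through.** **1. What is collected, and when**

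| Source | Adverse-event collection after ED discharge |
|---|---|
| Outcomes {12} | One email at 24–72 h |
| Table 2 {13} | None marked |
| Retention {18b} | None; index presentation and its records only |
| Post-trial care {30} | Review at about one week, for clinical care only |

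The first three rows cannot all be right. The fourth shows that a later clinical contact already exists and is unused for safety data.

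**2. The number behind a safety statement**

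The plan's sample size (margin 20 mm, SD 30 mm, one-sided alpha 0.025, power 80%, 5% attrition) reproduces:

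- n per arm = 2 × (1.960 + 0.842)² × 30² / 20² = 35.3, rounded up to 36, so 72 in total.
- 72 / 0.95 = 75.8, rounded up to 76, which is 38 per arm.

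If no event of a given kind is seen among 38 participants, the one-sided 95% upper bound on its rate is 1 − 0.05^(1/38) = 7.6%. That bound applies only to events apparent when the participant was asked, and it needs all 38 to have been assessed.

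**3. How much the window could matter**

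The documents give no onset time for either harm, so this step is an assumption shown as a range. With exponential onset and median m days, the share apparent by day t is 1 − 0.5^(t/m).

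| Assumed median onset (days) | By 24 h | By 72 h | By day 7 |
|---|---|---|---|
| 1 | 50% | 88% | 99% |
| 2 | 29% | 65% | 91% |
| 3 | 21% | 50% | 80% |
| 5 | 13% | 34% | 62% |
| 7 | 9% | 26% | 50% |
| 10 | 7% | 19% | 38% |

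The result depends almost entirely on the assumed median. With a median near one day, an enquiry at 72 h is adequate. With a median of several days, most events come later. Day 7 is better than day 3 on every row, but it is not complete if onset is slow. The table does not estimate what this trial would miss.

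**4. Direction**

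- Nerve injury is listed only for UGSCB, so missing it would flatter UGSCB.
- Counting residual block as an event at 24 h would count against UGSCB.
- Infection is listed for both blocks and the window is the same in both arms. Under-capture there lowers both observed rates and need not favour either.

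The net sign cannot be determined from the documents.

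**The case against.** The strongest reply is that calling the window too early is a clinical judgement the documents do not prove. They give no onset times and no block duration, and their remarks on prolonged analgesia are hedged. That stands, which is why the point is limited to what may not be apparent or distinguishable.

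A reader might be tempted by three stronger readings, none of which is supported:

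- **That day 1–3 covers 14–43% of the harms.** Those figures are 1/7 and 3/7, the timing of the email divided by the time to the clinic visit. They say nothing about the proportion of events seen.
- **That the observed rate would be about half the true rate.** This only restates an assumption that half of the events are recognised after day 3.
- **That the error runs towards declaring UGSCB safe.** Residual block counted as an event would push the other way.

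Other replies stand in part. Operations and manipulations elsewhere are collected after discharge and would catch some serious sequelae, but that item has no time window and is not an adverse-event assessment. Serious events go to the ethics committee within 72 h of notice, with no stated cut-off date, but someone must first learn of them. Following an ongoing event to resolution is detail that the full protocol may hold, so its absence here is not held against the plan. The contact window is different, because the article states it.

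It is also fair that a one-week check has limits. The limb may still be in plaster, a second email is still self-report, and with limited on-site orthopaedics (Study setting {9}) the review may take place elsewhere. Even with complete capture, 38 per arm cannot exclude uncommon harms. These limits argue against making clinic records the main safety source, but not against a second enquiry.

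**Conclusion.** The point holds as a low-cost improvement to a secondary outcome, together with a plain inconsistency to correct. It does not touch the primary pain comparison or the sample size.

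Certain from the documents: the 24–72 h email is the last stated adverse-event contact; Table 2 and {18b} do not show it; Table 3 names infection and nerve injury; and the one-week review is not used for adverse-event data.

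Judgement: that these harms may not be apparent, separable from residual block, or shown to persist at 24–72 h. The case is stronger for infection. For nerve injury, a deficit could be reported by then, but its persistence could not be judged.

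The amount and net direction of any under-capture are unknown. The 19–88% range at 72 h rests wholly on an assumed exponential onset with a median of 1 to 10 days.

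**What to change.** 1. Keep the 24–72 h email as it is.
2. Add a second adverse-event time point at about day 7 in both arms, putting the same email questions to every participant so that the method is standard across arms.
3. Supplement it by abstracting infection and new or persisting sensory or motor deficit from the record of the orthopaedic review already planned. These records add to the standard questions and should not replace them.
4. Report events by arm and time point, with the number assessed as the denominator each time.
5. Mark the post-discharge adverse-event contacts in Table 2 and amend {18b} so that both agree with {12}.

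**Cost.** A protocol amendment, a second email, and modest abstraction for 76 participants. No new visit or procedure and no change to clinical care or sample size are needed. Post-discharge transfers and operations are already being collected. Some records will be missing where review takes place elsewhere, and harms emerging after one week will still be missed.
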